## Methods

### Participants

#### Inclusion Criteria

The following inclusion criteria were applied to select autistic children: they had autism diagnosed by a child psychologist, were aged 7 to 12 years, were not already receiving systemic massage therapy, and were able to follow instructions. The children’s primary caregivers met the following criteria: they had been providing ≥1 year of childcare, were able to communicate with the massage trainer, and were able to read the questionnaire. Teachers met the following inclusion criteria: they served as primary caregivers for autistic children at school, had provided care for at least one semester, and were willing to participate in research.

#### Exclusion Criteria

This study applied exclusion criteria to 3 groups of people: the autistic children, their parents, and their teachers. For autistic children, the following exclusion criteria were applied: contraindications to TTM, such as fractures, fever, or psychoactive medication, and administration of other specialized interventions during the experimental period. Parents were excluded if they were not available at the allotted time. Further, teachers with insufficient time to complete the questionnaire were excluded.

#### Sample Size

The sample size calculation was based on research by Najafabadi et al [60]; no previous study has used both an autism massage intervention and the ATEC scale. The standard deviation of the social ATEC scores of the 2 groups was used to calculate the sample size needed to achieve a power of 80% and a 2-sided significance level of 5%. A dropout rate of 10% was assumed to determine the principal of intention for estimating the final sample size needed. According to a previously reported formula [61], a total of 48 participants were recruited for the study.

### Design and Setting

A randomized controlled trial (RCT) was conducted between February 2022 and June 2022. Participants were recruited from the Hainan Special Education School in Hainan Province, China. A recruiting poster and presentation were posted on the bulletin board at the school. Figure 1 depicts a flowchart of the study protocol prepared according to the SPIRIT (Standard Protocol Items: Recommendations for Interventional Trials) guidelines [62] (Multimedia Appendix 1). Before recruiting the participants, informed consent forms (Multimedia Appendix 2) were sent to the parents via the teachers, and if the parents agreed to participate, they signed the form and submitted it to a designated box within 2 days. The children with autism who could communicate with their parents also gave either verbal or written informed consent.

**Figure 1 figure1:**
[figure not shown]
Flowchart depicting the study design.

#### Randomization

Forty-eight participants (aged 7-12 years) from grades 1 to 6 were randomly assigned to parental TTM and control groups by random numbers generated with Online Research Randomizer (Geoffrey C Urbaniak and Scott Plous). The random numbers were then concealed in an opaque envelope.

#### Blinding

Since the massage intervention took place after school hours, parents brought their children to the health room, which is located far from the teaching building. Teachers were blinded to the group assignments of the children included in the study. Parents were asked to refrain from discussing the intervention to prevent contamination of the control group. Data collectors were also unaware of group placement.

### Ethical Considerations

This study complies with the ethical standards of the relevant national and institutional guidelines on human experimentation and was approved by the Khon Kaen University Ethics Committee for Human Research (HE642167). The study followed the Helsinki Declaration. Results will be published in a peer-reviewed journal and presented at domestic and international academic conferences to further promote communication. This protocol was registered with the Chinese Clinical Trial Registry (ChiCTR2100051355).

Researchers provided parents with information about the study and obtained informed consent from them while their children were in school. The parent or guardian signed the document and returned it to the school researcher or the teacher. Before the study, the parents were responsible for asking their children about their willingness to participate in the study. Children whose parents provided informed consent took part in the study. The researchers explained the study methods verbally to the children and parents and demonstrated the tests that would be performed on the children; the teachers and parents observed each child’s reaction to determine if the child consented or not before the test.

In the massage group, the participants were paid US $7 for each TTM session. In the control group, each volunteer participated in the evaluation 4 times and was paid US $7 each time. The decision was made that after data collection was finished, if good results were obtained in the parental TTM group, the control group would also be given training in TTM. Each teacher volunteer who participated in the 3 stages of assessment received US $30 for each stage.

### Intervention

Children assigned to the TTM group received sixteen 40-to-50-minute parent-delivered TTM sessions over an 8-week period (2 sessions per week) in the health room of the school after school had finished. Gifts and rewards were given to parents and children to increase intervention adherence rates. The control group maintained a normal daily routine when in school.

#### TTM Training

The parents of autistic children who were enrolled in the study took part in 3 TTM training sessions. Each 3-hour session was hosted by experts at the health room of Hainan Special Education School. Parents of participants in the intervention group were trained in TTM by an experienced traditional Thai masseur with a massage qualification until they became able to perform the experimental intervention. Thereafter, the massage trainer monitored the parents to ensure that they continued to perform TTM properly at each session.

#### TTM Procedure

The TTM method involves pressure massage and muscle stretching. Pressure massage involves massaging with the thumbs and pressing with the palms until slight muscle resistance is felt. The children may feel slight muscle tightness, but the massage should not be painful. The masseur will maintain pressure for 5 to 10 seconds and then release it to allow energy or blood to flow freely around the massage area; this is repeated 2 to 3 times for each body part. Muscle stretching includes the masseur observing the children and asking them whether they feel that the stretch is too deep; if the stretch is acceptable, they hold the appropriate position for 15 to 30 seconds [63]. The 9 steps of TTM are based on standard practice. However, they have been modified for this patient population: gentle touch is used to facilitate relaxation and promote social communication, motor control, and a sense of confidence in and love for the children. Starting from the head and continuing to the limbs easily promotes relaxation. Stretching at the end of the session is one of the principles of TTM.

In the starting position, the children lie on their side with the upper leg bent at the knee forming a 90° angle with a pillow placed under the head and a straight lower leg. The parent performing the massage kneels or sits behind the child. Massage strategies for distinct massage types should be performed as described in Table 1 and Figure 2.

**Table 1 table1:** Traditional Thai massage procedures for children with autism and the order in which they are performed.

Target area	Description of procedure
1. Neck (lateral position)	Massage is started in the neck region and extends along the back muscles toward the lumbar area. Massage is performed along the side of the neck toward the shoulders.
2. Back and waist	The paravertebral muscles, which are close to the thoracolumbar spine, are massaged toward the waist level. There are 3 lines of massage. One is started on the upper back near the spinous processes of T1 to L5 on each side of the back. The second line is about 1 cm along the side of the first one. The third line is about 1 cm along the side of the second one. A pressing massage style should be applied on the 3 lines, which should be initiated in the thoracolumbar region and continue toward the top of the sacrum.
3. Inner thigh (straightened legs)	Thumb pressure should be applied to the medial side of a straightened leg from the Achilles tendon toward the groin (along the line in panel 3 of Figure 1). This type of massage should be performed along 2 massage lines. The first massage line extends along the medial side of the leg, and the second massage line extends along the backside of the leg.
4. Outer leg massage (on the bent leg side):	Both hands are placed on the lower leg of the child. The lateral part of the lower leg should be pushed down using the thumb. This massage style should be applied from the area above the lateral malleolus and continued to the side of the knee joint. The top of both knees are pressed toward the middle of the hip. Outer leg massage should be performed along the 2 massage lines. The first line extends along the front of the leg, and the second line is positioned slightly behind the first line.
Repeat on opposite side	The child lies on the other side and procedures 1 to 4 are repeated.
5. Leg (supine position)	Massage is performed in front of the ankle to near the groin.
6. Leg massage (prone position)	Massage is initiated behind the heel around the Achilles tendon and continues toward the gluteal and hamstring muscles.
7. Arm	With the child in a prone position, thumb pressure is applied along the back of the lower and upper arm toward the shoulder. The procedure is then repeated on the other arm. In the supine position, push massage is applied upward from the center of the forearm and along the center of the arm toward the axilla.
8. Foot (supine position)	A foot massage is performed by applying pressure from the heel to all 5 toes. Then, the tip of each toe should be pulled gently.
9. Muscle stretch (the appropriate position is held for 15 to 30 seconds)	With the child in a supine position, the heel is stretched and the child’s foot is lifted until tension is felt. In the prone position, the child’s knees are flexed as much as possible by applying gentle pressure to the soles of the feet.

**Figure 2 figure2:**
[figure not shown]
Traditional Thai massage procedure: (1) neck massage, (2) back and waist massage, (3) inner thigh massage, (4) outer leg massage, (5) leg massage in the supine position, (6) leg massage in the prone position, (7, 8) arm massage, (9, 10) foot massage, and (11-13) muscle stretching. The procedure is performed in the numbered order.

### Fidelity

The fidelity measurement represents the number of times parents use massage with their children, incorporating any adjustments to the massage technique made by the expert. More than 90% attendance is expected, and the expert will correct improper technique in real time.

### Primary Outcome Measurement: ATEC

The ATEC questionnaire was developed by [name] and [name] M Edelson at the Autism Research Institute in the United States in the mid-1990s to help researchers and parents evaluate the effectiveness of various treatments for autistic children and adults [64]. It is not used to diagnose autism. It comprises 4 subscales: speech, language, and communication; sociability; sensory and cognitive awareness; and health and physical behavior. The maximum score is 179, with higher scores indicating autism of increased severity. The sensitivity and specificity of the Chinese version of the ATEC total scale and its subscales have been determined to range from 0.922 to 0.987 and 0.803 to 0.887, respectively; the scale has also been determined to have high reliability [65].

### Secondary Outcome Assessments

#### Gait

Gait was measured using a wearable BTS G-Walk device (BTS Bioengineering Company). Experimental gait data were collected at a frequency of 100 Hz and transmitted to a computer via a Bluetooth connection. All gait parameter measurements have been determined to have high test-retest and intertrial reliability (intraclass correlation coefficient: 0.728-0.969 and 0.84-0.99, respectively) [66,67]. Wireless internet was required for the gait tests, which were carried out on a flat surface that measured at least 10 × 10 m. Prior to performing the test, the height of the participant was entered, and an adjustable elastic band was placed around the participant’s waist. When taking the test, participants stood in place for a few seconds. After confirming that the sensor was connected to the computer via Bluetooth and the connection was stable, each child volunteer followed a marked 7-m path back and forth while walking normally. Teachers or parents were allowed to provide verbal cues but not physical assistance.

#### HRV Measurement

UBiomacpa (version 1; Biosense Creative) was used to detect the activity of the autonomic nervous system. The HRV test was carried out in an independent, quiet room at an ambient temperature of 26 °C. Before starting the test, the tester ensured that the equipment was properly connected. After receiving TTM, the autistic children were placed in a sitting position with a pulse sensor attached to their left index finger, and they underwent an HRV test for 2 minutes that was administered by a physiotherapist. When the test was complete, the device automatically generated a data report via a connected computer.

#### PSI-4-SF Assessment

The PSI-4-SF consists of 36 items in the following 3 dimensions: parent distress, parent-child dysfunction interaction, and difficult child [68]. The Chinese version of the PSI-4-SF has an internal consistency and reliability that ranges between 0.92 and 0.95 for each subscale. For the whole scale, the value is 0.97, indicating that this scale has good consistency and stability [69].

### Data Collection, Management, and Analysis

IBM SPSS (version 25; IBM Corp) will be used for data analysis. Missing outcome data will not be imputed in the analysis, but the multiple imputation method will be used to explore the potential impact of missing data on outcomes. Demographic data will be expressed as means with standard deviation and percentages. *P*<.05 will be considered statistically significant. Holm correction of *P* values will be applied for multiple comparisons to compare the immediate effects of TTM for autistic children and effects in the short and long term. The primary outcome is the ATEC score, which will use generalized estimating equations. Time will be the covariate and the model will include group, time, and the group × time interaction. A 2-tailed paired *t* test or Wilcoxon signed-rank test will be used to test ATEC score, HRV, and gait parameters, as well as PSI-4-SF score changes within each group after testing for normal distribution. The relationship between physiological effects and ATEC results will be evaluated using a correlation test. A coefficient value <0.4 indicates a low degree of correlation, a value between 0.4 and 0.7 indicates a medium degree of correlation, and a value >0.7 indicates a high degree of correlation between variables.

Two trained assessors will be responsible for data collection, electronic double entry of the data, and management of the database. A team from the Key Laboratory of Data Science and Smart Education at Hainan Normal University, which is independent of the study team, will be responsible for data monitoring.

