Furthermore, the refractory and lifelong nature of autism has profound implications for parents of autistic children and evidence shows that parents of children with autism experience more parenting stress than parents of nonautistic children or children diagnosed with other disabilities [55,56]. One recent review suggested that family-based interventions for mental disorders in children are becoming increasingly important, with more positive outcomes when parents are involved in the treatment [57]. Previous research revealed that parents who engaged in a massage-based intervention not only satisfied family-based care needs [58] but also showed relieved anxiety [42] and strengthened parent-child bonding [37,38,59]. The effects of TTM delivered by the parents of autistic children on these outcome measures have not been verified. This study aims to assess the effects of parental-delivered TTM in children with autism by evaluating changes in symptoms and physiological parameters (ie, gait and HRV). The primary objective of the study is to assess the effectiveness of parental TTM in improving symptoms of autism according to the Autism Treatment Evaluation Checklist (ATEC). Secondary objectives are to evaluate instant and cumulative effects of the parental TTM intervention via an assessment of gait and HRV and explore the relationship between symptom improvement and observed changes in physiological parameters. The tertiary objective is to examine changes in levels of parental stress after parents have administered the TTM intervention. The following four research questions will be addressed: (1) Do core symptoms significantly improve (ie, does ATEC score improve) in autistic children after parental TTM in comparison with the control group? (2) Do HRV and gait indicators significantly improve in children with autism after parental TTM? (3) Is ATEC score improvement related to observed changes in physiological parameters? (4) How does parental stress change throughout the intervention period, as measured by the Parenting Stress Index, Fourth Edition–Short Form (PSI-4-SF)?

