## Results

We finished all data collection on June 20, 2022. Data analysis will be started, and we expect results to be published in 2023. The normal distribution of the data will be determined before descriptive statistics for all variables are calculated. The participants’ demographic information will be reported as descriptive data. The primary outcomes will be expressed as continuous variables, and generalized estimating equations will be used to evaluate the effect of TTM on the children (via the ATEC score) at 3 time points: immediate, short term, and long term. Changes in physiological parameters (ie, HRV and gait parameters) after the intervention will be analyzed. Further, the relationship between ATEC score and physiological parameters will be identified with a correlation analysis. Finally, changes in parental stress throughout the intervention period will be investigated with the PSI-4-SF.

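### The Holm correction is described for comparisons over time, while research question 2 rests on an undesignated set of HRV and gait parameters, so false-positive risk across parameters is materially inflated unless the family is widened or key parameters are named

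*Protocol article*

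**What the plan says.** All references are to the Protocol article.

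- **Threshold.** Data Collection, Management, and Analysis states that P "<.05 will be considered statistically significant".
- **Multiplicity rule.** The same section states that Holm correction "will be applied for multiple comparisons to compare the immediate effects of TTM for autistic children and effects in the short and long term". Results uses the same three terms for the ATEC analysis, "at 3 time points: immediate, short term, and long term". The rule does not say which outcomes it covers.
- **Tests for HRV and gait.** Paired t or Wilcoxon signed-rank tests are planned for ATEC, HRV and gait, "as well as PSI-4-SF score changes within each group after testing for normal distribution".
- **Question to be answered.** Research question 2, at the end of Prior Work, is "Do HRV and gait indicators significantly improve in children with autism after parental TTM". HRV and gait belong to the secondary objectives.
- **What is measured.** HRV Measurement says that "the device automatically generated a data report via a connected computer". The Gait section speaks of parameters in the plural. Results adds "Changes in physiological parameters (ie, HRV and gait parameters) after the intervention will be analyzed". No HRV index or gait parameter is named in any of these places, and none is given priority.

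**The concern.** Tests on the secondary outcomes multiply in two directions: over time points and over parameters. The correction is described for the first. Nothing in the article deals with the second, although research question 2 is put as a question of statistical significance about two groups of indicators. The article also gives no rule for turning several parameter results into one answer.

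HRV and gait are secondary, but they carry the trial's distinctive claim. The Abstract faults prior studies for lacking objective indicators and mechanisms, and the Discussion promises objective indices to explore mechanism. ATEC is rated by the parents who give the massage and by blinded teachers, so a device-based result would carry particular weight with readers. A single nominally significant index from a set of unstated size could be read as physiological confirmation when the massage has no effect on either system.

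**Working it through.** **Figure to reproduce.** There is none. The article gives no familywise error rate and no count of HRV or gait tests. The sample size of 48 was derived from ATEC social scores and does not bear on this point.

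**Inputs from the article.** Significance level 0.05; two-tailed tests; three comparisons over time; 48 children allocated 1:1, with 10% dropout assumed.

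**Assumptions.** The total number of HRV and gait parameters tested, k, is 5, 10 or 20. The pairwise correlation between parameters is 0, 0.5 or 0.8. For the simulation, there are 22 children in one group (24 × 0.9 = 21.6), and HRV and gait are each tested at three time points correlated 0.5.

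**Step 1: any false positive, independent parameters, each held at 5%.** Formula: 1 − 0.95^k.
- k = 5: 1 − 0.95^5 = 0.226
- k = 10: 1 − 0.95^10 = 0.401
- k = 20: 1 − 0.95^20 = 0.642

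With normal test statistics correlated at 0.5 (200,000 draws), the results are 0.182, 0.288 and 0.420.

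**Step 2: false improvements alone.** Half of each two-sided 5% lies in the favourable direction, so the formula is 1 − 0.975^k.
- k = 5: 0.119
- k = 10: 0.224
- k = 20: 0.397

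**Step 3: the rule simulated.** Paired t tests were run within one group, with Holm over the three time points inside each parameter. With no true effect, a parameter yields a rejection when its smallest P is at most 0.05/3 = 0.0167.

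| k | Correlation | Any false positive | False improvement | Holm over all 3k tests, any false positive |
|---|---|---|---|---|
| 5 | 0 | 21.0% | 11.4% | 4.6% |
| 5 | 0.5 | 17.9% | 8.9% | 4.3% |
| 5 | 0.8 | 13.0% | 6.4% | 3.1% |
| 10 | 0 | 37.0% | 20.7% | 4.5% |
| 10 | 0.5 | 28.8% | 14.7% | 4.2% |
| 10 | 0.8 | 17.7% | 8.7% | 2.6% |
| 20 | 0 | 61.0% | 37.5% | 5.0% |
| 20 | 0.5 | 43.3% | 22.5% | 4.1% |
| 20 | 0.8 | 24.7% | 12.5% | 2.2% |

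With independent parameters, the simulated values lie slightly below those of Steps 1 and 2, because Holm over correlated time points spends a little less than 5% per parameter. The last column shows that widening the family restores control, at 2.2% to 5.0%.

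**Step 4: when would an error be more likely than not?** With independent parameters, the chance of any false positive passes 50% at k = 14 (1 − 0.95^14 = 0.512). For a false improvement it takes k = 28 (1 − 0.975^28 = 0.508). At a correlation of 0.5, neither reaches 50% even at k = 20.

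**The case against.** The strongest case against runs as follows. The Holm sentence mentions comparisons over time but does not exclude a wider family. An article commonly leaves the list of device indices and the ordering of secondary outcomes to the full protocol or analysis plan, which is not shown. Control of familywise error across secondary, mechanistic measures is partly convention. The parameter count and the correlation are both assumed.

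Much of this stands, and it limits what can be said. A reader might infer any of the following, and the documents support none of them:

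- **That correction across parameters is ruled out.** The sentence is open on this; it leaves the family undefined beyond time.
- **That every value the devices print will be tested.** The remark about the automatic report describes equipment and does not define endpoints.
- **That a false finding of improvement is likely.** With 10 to 20 parameters correlated at 0.5, the simulated risk is 15% to 22%. Step 4 shows how many parameters a figure above 50% would need.
- **That one significant index is declared sufficient for a positive answer.** The article sets no such criterion. The figures above give the chance that at least one parameter is falsely significant, which is what an undefined criterion leaves open.
- **That the correlation cut-offs of 0.4 and 0.7 act as a test for question 3.** They are labels of strength, and the article does not say how many children enter the correlations.

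The objection does not remove the point. A missing parameter list would be no finding by itself. Here the article does state a multiplicity rule, and the comparisons it describes leave out the dimension in which the secondary tests multiply.

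**Conclusion.** The point holds as a gap in the stated multiplicity rule for a secondary objective. If Holm is applied over time points alone, error across HRV and gait parameters is materially inflated. Even at five independent parameters, the chance of a false improvement is 11.9% against a nominal 2.5%, and the chance of any false positive is 22.6% against 5%. Across the simulated range of 5 to 20 parameters and correlations of 0 to 0.8, the chance of any false positive is 13% to 61%.

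These figures rest on the assumed parameter counts and correlations, on no true effect, and on the reading that Holm reaches the HRV and gait tests over time and goes no further. The primary ATEC analysis by generalized estimating equations is a separate analysis and is not affected. The change is worth making but does not threaten the trial's main conclusion.

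**What to change.** Before the HRV and gait data are analysed, add a dated statement that does the following:

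1. **Define the family for question 2.** Either designate the key HRV and gait parameter(s), with Holm over these and their time points, or extend Holm across all tested HRV and gait parameters and their time points.
2. **Base the claim on between-group comparisons.** A change within the massage group cannot be separated from the passage of time or repeated testing, so the control group should enter the test.
3. **Label the rest exploratory.** Report all undesignated parameters and the question 3 correlations with estimates and 95% confidence intervals, without a significance claim.

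The article reports that data collection is finished and that analysis has yet to start, so no new data are needed. Because device reports already exist, the choice should be made without sight of results by group. If that is no longer possible, all HRV and gait results should be labelled exploratory.

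The cost is a stricter threshold for the key parameters and no confirmatory claim for the others. For example, with one HRV index and one gait parameter at three time points, the smallest P would be compared with 0.05/6 = 0.0083. With 10 parameters all kept in the family, it would be compared with 0.05/30 = 0.0017. Designating a few parameters is therefore the cheaper route in power.

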**Methods:**

A 2-armed, parallel randomized controlled trial was conducted between February 2022 and June 2022. Forty-eight children with autism (aged 7-12 years) were recruited from the Hainan Special Education School and randomly assigned to either a parental TTM or control group at a ratio of 1:1 based on random numbers generated with Online Research Randomizer. The generated sequences were concealed in an opaque envelope. Individuals in the parental TTM group received 16 parent-delivered TTM sessions over 8 weeks at the school’s health room after school, and the control group maintained a normal daily routine. Outcomes were assessed on admission, after 8 weeks, and at a 2-month follow-up and included the effect of massage treatment on autism symptoms, measured with the Autism Treatment Evaluation Checklist score (evaluated by parents and a blinded teacher), physiological parameters (ie, heart rate variability and gait), and the Parenting Stress Index, Fourth Edition–Short Form.

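### The primary GEE for ATEC lists no baseline ATEC covariate; adding it is a free improvement that lowers the variance of the group contrast by 5% to 25% (assumed correlation 0.9 to 0.5)

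*Protocol article*

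**What the plan says.** Under Data Collection, Management, and Analysis the article says: "The primary outcome is the ATEC score, which will use generalized estimating equations". It then names the terms: "the model will include group, time, and the group × time interaction". Time is called the covariate; whether it is categorical or linear is not said. No variance estimator, working correlation or reference distribution is given. On missing data: "Missing outcome data will not be imputed in the analysis", with multiple imputation used to explore the impact of missing values.

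The Abstract puts the ATEC assessments on admission, after 8 weeks and at a 2-month follow-up. The Results section lists the three GEE time points as immediate, short term and long term, without naming baseline.

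Under Sample Size the targets are "a power of 80% and a 2-sided significance level of 5" per cent. "A dropout rate of 10% was assumed", and "a total of 48 participants were recruited for the study". Children were "randomly assigned to either a parental TTM or control group at a ratio of 1:1". For the variance input, "The standard deviation of the social ATEC scores of the 2 groups was used to calculate the sample size", but neither that SD nor the difference to be detected is given.

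**The concern.** The term list is a stated choice for the primary outcome, and it leaves out the variable most likely to predict follow-up ATEC, which is already collected. With about 43 analysable children, precision is scarce. A contrast that uses baseline only by subtraction, or not at all, has a larger variance than one that adjusts for it. What is at stake is power and interval width for the main result.

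A second, smaller matter follows from the trial's size. Robust GEE standard errors rest on a large number of independent children. At 21 to 24 per arm, the uncorrected version with a normal reference is mildly too optimistic, so the correction is worth naming when the model is revised.

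**Working it through.** **Inputs from the article.** Total 48, 1:1, so 24 per arm; dropout 10%; two-sided 5%; power 80%; ATEC at admission, 8 weeks and 2 months.

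**Assumptions.** Correlation rho of baseline with follow-up 0.5 to 0.9; equal SD at each visit and equal correlation between visits; normal, complete data; categorical time; difference of 0.6 SD for the power figures.

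**Step 1: the plan's own figure.** With no SD or difference given, 48 can only be solved backwards. From d = (1.960 + 0.842) × √(2/n), n = 21 per arm gives d = 0.86, and 21/0.9 = 23.3, rounded up to 24 per arm, or 48. A total of 43 also gives 43/0.9 = 47.8, or 48. So 48 is attainable with an implied difference of about 0.84 (n = 22) to 0.86 SD (n = 21), but cannot be checked forwards. After dropout, 48 × 0.9 = 43.2 children, about 22 per arm.

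**Step 2: precision.** If admission is a level of time, group × time at a follow-up visit is the difference in mean change. Taking the variance of one ATEC measurement as 1, the per-child variances are:

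- change contrast: 2(1 − rho)
- baseline-adjusted contrast: 1 − rho²
- ratio: 2(1 − rho)/(1 − rho²) = 2/(1 + rho)
- follow-up only, baseline outside the model: 1, so the ratio is 1/(1 − rho²)

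| rho | change | adjusted | change/adjusted | follow-up only/adjusted |
|---|---|---|---|---|
| 0.5 | 1.00 | 0.75 | 1.33 | 1.33 |
| 0.7 | 0.60 | 0.51 | 1.18 | 1.96 |
| 0.8 | 0.40 | 0.36 | 1.11 | 2.78 |
| 0.9 | 0.20 | 0.19 | 1.05 | 5.26 |

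Seen from the other side, adjustment lowers the variance of the change contrast by 25%, 15%, 10% and 5%.

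**Step 3: power at 22 per arm, 0.6 SD.** Standard error = √(2/22 × per-child variance). Power is from simulation (40,000 trials per setting), both analyses with a t reference and the change contrast with a variance corrected for degrees of freedom.

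| rho | SE change | SE adjusted | power change | power adjusted |
|---|---|---|---|---|
| 0.5 | 0.302 | 0.261 | 49% | 60% |
| 0.7 | 0.234 | 0.215 | 71% | 77% |
| 0.8 | 0.191 | 0.181 | 87% | 89% |
| 0.9 | 0.135 | 0.131 | 99% | 99% |

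**Step 4: type I error if no correction is used.** For a saturated group × time model, the uncorrected sandwich divides by n rather than n − 1. At n = 22 the standard error is too small by the factor √(21/22) = 0.977. The nominal cut-off of 1.960 then acts as 1.960 × 0.977 = 1.915 on a t distribution with 42 degrees of freedom, which gives 6.2%. The same calculation gives 6.3% at 21 and 6.1% at 24 per arm. In simulation the 2-df group × time Wald test gives about 7.0% to 7.3% at 22 per arm.

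What repairs this, by simulation at 22 per arm:

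- unadjusted contrast, corrected variance, t reference: about 4.9%
- baseline-adjusted contrast, t reference: about 4.9%
- baseline-adjusted contrast, normal reference: about 5.6%

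The small-sample reference restores the error rate. Baseline adjustment alone does not.

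**The case against.** **The gain may be small.** No correlation is given, and if ATEC is very stable the gain nearly vanishes: 5% in variance and nothing visible in power at rho 0.9. This stands, and is why the full range is shown. The variance is still lower throughout it.

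**Baseline is already used.** If admission is a level of time, the interaction compares change from baseline. This stands too: it would be wrong to say that the plan ignores baseline, or that the analysis is invalid. A reader might infer from the time points in the Results section that baseline is outside the model. The Abstract counts admission among its three assessments, so the article does not settle this. If it were so, the loss would be larger for rho above 0.5.

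**The planned p values are too small.** A reader might infer this from the choice of GEE at this size. The article names no variance estimator or reference distribution, and such detail may sit in an analysis plan not shown. The 6.1% to 6.3% is conditional on an uncorrected sandwich with a normal reference. The figure near 7% belongs to a 2-df test that the article does not name as its decision rule.

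**Dropout will bias the primary estimate.** This is tempting because a GEE on available data generally needs data missing completely at random. But simulated dropout of about 10% driven by baseline score in the same way in both arms gave a bias of 0.000 SD (rho 0.5) and −0.002 SD (rho 0.7). It took opposite mechanisms in the two arms to reach 0.09 to 0.12 SD. Multiple imputation is already planned to examine missing data.

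**The change comes late.** Data collection ended on June 20, 2022. However, the article reports analysis as still to start, so a prespecified covariate can be fixed without knowledge of the results. Replacing the GEE altogether is a matter of preference.

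**Conclusion.** A free improvement. The listed model forgoes baseline ATEC as a covariate. With admission as a level of categorical time, this costs 5% to 33% in variance for rho 0.9 to 0.5, and up to 11 percentage points of power at 22 per arm and 0.6 SD. The size rests on the assumed rho, equal variances and correlations across visits, and categorical time; with linear time the interaction would be a difference in slopes and these ratios would not apply directly.

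The article does not show an inflated type I error, a biased estimate or a need to abandon GEE. The small-sample correction belongs with the change because its absence would matter modestly at about 43 children.

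**What to change.** Before analysis starts, fix the primary model as follows.

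- Outcome: ATEC at 8 weeks and at 2 months.
- Terms: group, categorical time, group × time, and admission ATEC as a covariate. This also settles whether baseline is a time level or a covariate.
- Method: keep the GEE; a linear mixed model is an acceptable alternative.
- Small-sample correction: bias-corrected sandwich with a t reference for the GEE, or Satterthwaite degrees of freedom for the mixed model.
- Missing data: keep the planned multiple imputation as the sensitivity analysis.

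Cost: a dated change of model wording, with no new data, since baseline is already collected. Intervals will be slightly wider than an uncorrected GEE would print. Confirm that the named software (SPSS 25) offers the chosen correction. Because data collection has ended, record that the change was made before any comparison by group, and report the model as published alongside it.
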